### Data Analysis

Analysis will be performed with Stata software (StataCorp LLC). Continuous variables will be reported as mean and standard deviation (or in case of nonnormal distribution as median and interquartile range). Categorical variables will be displayed as frequencies or proportions. The association between food security status, dietary data, and health outcomes will be assessed through chi-square analysis of baseline data.

To assess the effect of the interventional program on food security, dietary intake, nutritional status and body composition, quality of life, muscle strength, fatigue scale, physical activity habits, and serological markers of cardiovascular risk, 2-tailed *t* tests will be used to compare the amount of change within each group (baseline, end of study [at 3 months] and follow-up [at 6 months]). Independent sample *t* tests will be used to compare the intervention group and control group on the same outcomes.

Dietary intake assessed with 2-day 24-hour recall will be analyzed according to the recommended number of servings from each food group of the Portuguese Food Wheel [37]. Intakes of micronutrients that tend to be low in vulnerable population groups (iron, calcium, folate, and vitamins A, C, and D) will be also analyzed. The percentage of individuals meeting the Estimated Average Requirement or Adequate Intake for iron, calcium, folate, and vitamins A, C, and D will be calculated [38]. Food Processor Nutrition Analysis software (ESHA Research) will be used to estimate the intakes of energy, macro-, and micronutrients.

The association between each outcome and the candidate covariables will be performed using generalized models. We will use multivariate logistic and linear (according to the outcome) regression models. The candidate covariates will be first analyzed by univariate regression. Covariates will enter the multivariate models if their *P* value is less than .25 in univariate analysis or considered clinically relevant in this setting. The selection of covariates will be stepwise by backward selection, according to the level of significance (<.05). Multilevel analysis and sensitive analysis will be performed when appropriate.

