A nutrition and physiotherapy assessment will be performed at baseline and end of intervention assessment (at 3 months). The nutritionist will collect data regarding food insecurity (Household Food Insecurity Scale [HFIS] adapted from the US Department of Agriculture Household Food Security Survey Module [21]), dietary habits (2-day 24-hour diet recall, Prevención con Dieta Mediterránea [PREDIMED] index [31], and food frequency questions), anthropometric data (height, weight, and waist circumference), body composition data obtained by bioimpedance (fat mass, fat-free mass, total body water), attitudes and barriers on diet, food expenses, and other resources for food. Regarding the dietary habits assessment, a second 24-hour diet recall will be performed by phone call interview performed within 1 week.

Physiotherapy assessment will be conducted aiming at collect data regarding physical activity (Elderly Mobility Scale [EMS] [32] and International Physical Activity Questionnaire [IPAQ]) and muscle strength (hand grip, knee extension, and hip flexion by using a dynamometer). The assessment scales used in the study are all Portuguese-validated versions, and the average time for the evaluation will be 90 minutes.

The nurse will perform a structured questionnaire in order to capture baseline knowledge on healthy lifestyles. This questionnaire will be repeated during the 3-month and 6-month follow-up assessments.

Blood samples will also be collected in order to obtain data regarding the nutritional status and serological biomarkers of cardiovascular risk (albumin and prealbumin levels, insulin resistance, cholesterol levels, hemoglobin A_1c_, adipocytokines, high sensitivity C-reactive protein, interleukin 1, interleukin 6, and tumor necrosis factor).

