### Sample Size

Sample size was estimated considering a *t* test (independent samples) for comparing the mean change in food insecurity score from baseline to the end of study between group 1 (intervention) and group 2 (control). The intervention is considered to be meaningful if 50% of the individuals in group 1 have a decrease of 1 point in the food insecurity score, all the remaining being unchanged. This results in a difference of –0.5 between the mean changes of the 2 groups. Standard deviation of the change is assumed to be 1.5. Power is set at 0.80 and α=.05. We expect to include and randomize 141 experimental and 141 control elderly people with food insecurity (n=282) equally distributed among the 17 primary care centers. We are prepared to recruit around 70 individuals in each primary care center (a total of 1128 subjects are needed) because we assume that 50% (based on the INFOFAMÍLIA [National Survey on Food Insecurity in Portugal] survey) [36] of the target individuals are food insecure and that 50% of those will adhere to the study.

Of note, the standard approach to sample size calculation based on a clinically important difference was not possible to use in this study because data on interventions in food insecurity are scarce. We have considered the referred effect size based on the INFOFAMÍLIA survey data. In this study, the majority of Portuguese food-insecure households are in low food insecurity level (39.8%), and about 80% of those in the low food insecurity level obtained just 1 point in the food insecurity score, which means that if our intervention decreases the food insecurity score by 1 point we will be able to see a change from the low food insecurity level to the food security level.

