### Randomization, Allocation, and Blinding

Randomization will be computer generated. Randomization will be stratified according to gender and food insecurity level (low/moderate vs severe) with permuted blocks of six. Subjects will be allocated to the study group versus control with a probability of 1:1.

We will ensure researchers taking follow-up outcome measures will be blinded to group allocation; after randomization, the intervention group will be informed that they will have access to the intervention program (TV app) by an independent assessor (single-blind).

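### The baseline association analysis assigns chi-square to all dietary and health measures, many of them continuous or ordered; for moderate associations this costs about 20 to 35 points of power, under assumptions the protocol does not supply

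*Protocol article*

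**What the plan says.** The Data Analysis section names a single test for the cross-sectional baseline question: "The association between food security status, dietary data, and health outcomes will be assessed through chi-square analysis of baseline data". It sets no cut-points or number of categories and mentions no trend version of the test.

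The Data Collection section shows what falls under dietary data and health outcomes. The nutritionist records "dietary habits (2-day 24-hour diet recall, Prevención con Dieta Mediterránea [PREDIMED] index [31], and food frequency questions), anthropometric data (height, weight, and waist circumference" and bioimpedance measures. Other items are EQ-5D-3L, FACIT-F, HAQ, HADS, muscle strength by dynamometer and blood markers. Some items are categorical from the start, such as self-reported chronic diseases. Data Analysis also plans the percentage of participants who meet micronutrient requirements.

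Food insecurity is a numeric HFIS score with ordered levels. The only grouping that the article fixes is the one used for allocation: "Randomization will be stratified according to gender and food insecurity level (low/moderate vs severe". It does not say which grouping the baseline analysis will use.

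Later in Data Analysis, linear or logistic regression, chosen by outcome, is planned for relating outcomes to candidate covariables. Those covariables are not listed.

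**The concern.** A Pearson chi-square test works on a contingency table. To use it on grip strength, albumin or FACIT-F, the analyst must first cut the measure into groups. The test then treats those groups, and the food-insecurity levels where there are more than two, as unordered. Three things follow for the continuous and ordered measures:

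- A graded association of moderate size is missed more often than it need be.
- The result depends on cut-points that the article does not state.
- The analysis yields no mean difference and no slope per HFIS point.

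The Introduction says that food insecurity has been less well studied in the elderly, so these baseline associations have some scientific value of their own.

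**Working it through.** **The plan's own figure.** The only sample-size calculation is for the primary comparison. Its inputs, from the Sample Size section, are "This results in a difference of –0.5 between the mean changes of the 2 groups", "Standard deviation of the change is assumed to be 1.5" and "Power is set at 0.80 and α=.05". A two-sided test is assumed here; Data Analysis says two-tailed only for the within-group tests ("2-tailed *t* tests will be used to compare the amount of change within each group").

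n per group = 2 × 1.5² × (1.960 + 0.842)² / 0.5² ≈ 141.3. This rounds up to 142. At the stated 141, power is 79.9% (79.7% with the noncentral t), so the figure is reproduced. It gives the N used below, from "We expect to include and randomize 141 experimental and 141 control elderly people with food insecurity (n=282) equally distributed among the 17 primary care centers", and says nothing about the power of the baseline association.

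**Assumptions for the baseline test** (none is in the article):
- Food insecurity and the other measure follow a latent bivariate normal distribution with correlation ρ.
- Status is cut into two levels (50/50 or 75/25) or three (60/25/15 or thirds).
- For chi-square, the other measure is cut into k equal groups.
- N = 282, two-sided α = .05.

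**Formulas.**
- Uncut test (t test for two levels, linear trend for three): r = ρ × Cov(level score, latent status) / SD(level score). Power ≈ Φ(atanh(r) × √(N − 3) − 1.960).
- Chi-square: noncentrality = N × Σ(P − E)²/E, where P is the cell probability and E the product of its margins; df = (levels − 1)(k − 1).

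**Example 1: two levels 50/50, median cut, ρ = 0.20.**
- Uncut: r = 0.20 × √(2/π) = 0.1596. Then atanh(0.1596) × √279 = 2.688, and Φ(2.688 − 1.960) = 76.7%.
- Chi-square: noncentrality = 282 × [(2/π) × arcsin(0.20)]² = 282 × 0.01643 = 4.63 on 1 df, power 57.6%.
- Loss: 76.7 − 57.6 = 19.1 points.

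**Example 2: three levels 60/25/15, ρ = 0.20.**
- Uncut trend: r = 0.1674 and atanh(r) × √279 = 2.82, power 80.6%. The squared signal, 2.82² ≈ 7.97, sits on 1 df.
- Chi-square: noncentrality 5.11 on 2 df (k = 2), 6.38 on 4 df (k = 3), 6.93 on 6 df (k = 4). Powers are 51.3%, 49.7% and 46.3%.
- Finer cutting recovers signal but spreads it over more degrees of freedom, so power does not recover.

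**Benchmark case: ρ set so that the uncut test has 80% power, N = 282.**

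| Status levels | k = 2 | k = 3 | k = 4 | Loss (points) |
|---|---|---|---|---|
| Two | 61% | 60% | 57% | 19 to 23 |
| Three | about 50% | 49% | 45–46% | 29 to 35 |

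With N = 1128 (all those screened), the losses at the same benchmark agree within 0.3 points.

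**Sensitivity to the benchmark (two or three levels, k = 2 to 4, N = 282).**

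| Strength of association | Loss (points) |
|---|---|
| ρ = 0.05 | at most about 5 |
| Uncut power 60% | 17 to 31 |
| Uncut power 90% | 16 to 31 |
| Uncut power 95% | 12 to 25 |
| Uncut power 99% | 5 to 13 |
| ρ = 0.40 | at most about 2 |

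**Sensitivity to the comparator.** In the three-level benchmark case, one-way ANOVA, which also ignores the order of the levels, has about 70% power. Against it the chi-square loss is about 19 to 26 points.

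**The case against.** **The cutting is inferred.** The article states no categories, and the term it uses, status, is itself categorical. Self-reported diseases and the share meeting micronutrient requirements need no cutting, and chi-square suits them. This stands, and it limits the point to continuous and ordered measures. For those, cutting follows from the test named.

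**The regression models may cover the same ground.** They could recover part of the information. But they relate outcomes to unlisted covariables and do not name food security status as an exposure, so they cannot be read as replacing the stated test.

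**The article is condensed, and test choice by variable type belongs in a fuller plan.** That would answer an omission. Here a test is named for the whole association without qualification.

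**Stronger readings that a reader might infer, and that the document does not support:**
- *A fixed loss of 20 to 35 points.* The article gives no correlation, level split or power for this analysis. That range belongs to the 80% benchmark; the loss nearly vanishes at both extremes of strength.
- *A loss as large as 56 points.* This arises with an assumed 79/14/7 split at ρ = 0.20, from comparing Spearman power of about 90% with chi-square power of 34% (quartile cut). The 90% treats HFIS as fully continuous. The Sample Size section says about 80% of those at the low level scored exactly 1 point. With those ties imposed, Spearman power is about 78% and the gap about 78 − 34 = 44 points.
- *The same loss for any grouping.* The only grouping fixed in the article has two levels. No order of status is then ignored, and the loss is at the lower end.
- *Damage to the trial's main result.* This association is not a stated outcome, and the group comparisons use t tests.

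**Conclusion.** The point holds as a minor one. The article assigns chi-square to the whole baseline association, and for the continuous and ordered measures that means cutting them and ignoring their order. For a moderate association (uncut test at about 80% power, N = 282, two-sided α of .05), the cost is roughly 20 points of power with two status levels and 30 to 35 with three ordered levels. These figures rest on an assumed latent normal model, level splits and cut-points, and they shrink to a few points for very weak or strong associations. For items that are categorical by nature there is no cutting and no such loss. The primary outcome, the randomised comparison and the total of 282 are unaffected.

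**What to change.** Replace the chi-square sentence in Data Analysis with wording such as:

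> Baseline HFIS score or food-insecurity level will be related to continuous and ordered dietary and health measures on their full scale, by t test or ANOVA, linear trend, Spearman correlation, or linear or ordinal regression as the measure requires. Chi-square tests will be used for variables that are categorical by nature, such as self-reported disease or meeting a micronutrient requirement. Cross-tabulations by level will be descriptive.

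It would also help to state which food-insecurity grouping this analysis uses. The cost is a sentence or two of text, with no new data, visits or participants. The downside is slightly less simple reporting: slopes, mean differences or correlations in place of cross-tabulations alone.

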According to the internationally recognized definition, “food security is the situation that exists when all people, at all times, have physical and economic access to sufficient safe and nutritious food that meets their dietary needs and food preferences for an active and healthy life” [6]. In contrast, food insecurity is a broad concept that includes attributes related with the uncertainty or worry about food, inadequate quality of food, inadequate quantity of food, food acquired through socially unacceptable means, and lack of consistent access to adequate food [7]. Food insecurity is often associated with economic constraints. The rates of food insecurity have been rising worldwide [7]. While the United States is one of the wealthiest nations in the world with a rich and abundant supply of food and resources, 14.3% of US households were food insecure at some point during 2013 [8]. A study of Portuguese primary care center attendees in 2013 showed that 50.7% were food insecure [9]. Furthermore, more than one-third of Portuguese adults with food insecurity are overweight (41.0% in moderate food insecurity and 37.7% in severe food insecurity categories) [10]. This situation needs particular attention if we consider that Portugal is one of the Organization for Economic Cooperation and Development countries with highest levels of income inequalities [11].

Food insecurity has been shown to be associated with poor self-rated health and several noncommunicable diseases such as diabetes, hypertension, fibromyalgia, and osteoporosis [12,13].

In general, food insecurity has been less well studied in the elderly. Data from the United States suggested that food insecurity decreases as age increases. The prevalence of food insecurity was 20.4% among US adults aged between 40 to 49 years and 15.7% among older adults aged between 60 to 69 years [14]. The same trend was observed for Canada: the prevalence of food insecurity was lower in elderly people (16% vs 29% for the total sample) [15]. However, the nutrition and health consequences might be potentially more severe for older adults. In elderly populations, food insecurity might occur as a result of other factors rather than constraints of financial resources. There is evidence that food insecurity among the elderly can be associated with health or mobility problems (functional impairment), which can also compromise the access to healthy food.

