Indeed, the concept of food insecurity in elderly persons also includes nutritional deficits and other relevant aspects related with limited or inability to use food due to functional impairments and health problems [16,17]. For older adults, who generally require special attention for optimal nutrition, food insecurity has been a risk factor for poor nutritional status and low muscle power especially in those with physical disabilities, increasing hospitalizations and death [4,5].

Information and communication technology (ICT) solutions can be used as a personalized cost-effective smart model of health empowering subjects to take more responsibility for their own health and quality of life. Moreover, ICTs have the potential to make a major contribution to improve access to quality services while controlling costs. Elderly people spend a significant amount of time watching television (TV) [18], which can be used as a tool to improve health literacy and a vehicle for promoting health lifestyles. Promoting healthy lifestyles in elderly populations is crucial to slow physical decline and improve well-being, delay the deterioration of health, and reduce the risk of mortality [19].

For this study, we hypothesized that a home-based intervention program on dietary and physical activity through a TV app will improve food security as well as clinical endpoints such as nutritional status, body composition, balance, strength, and quality of life in the elderly population. Considering the broad definition of the food insecurity concept and its 4 main dimensions (availability of food, physical and economic access to food, food utilization, and stability of the other dimensions) [20], our intervention program will be focused on the dimension of food security related to the use or utilization of food, which might be affected by literacy in food and health. Our hypothesis is that a TV-based intervention might have a large potential in promoting healthy lifestyles among low socioeconomic status groups and for people with low literacy, since TV is the most frequently used ICT by low literacy people.

This paper describes the study protocol of a home-based randomized controlled trial aimed at evaluating the impact of a TV-based intervention on healthy lifestyle promotion in elderly subjects in food insecurity reduction.

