### Eligibility

To be eligible for this randomized controlled study, subjects must fulfill all of the following inclusion criteria: (1) aged 60 years or older, (2) identified as food insecure in the recruitment [21], (3) able and willing to give written informed consent and phone number contact and comply with other requirements of the study protocol, (4) Portuguese speaker or able to understand Portuguese, (5) noninstitutionalized and living in a private household in Portugal, (6) have electricity at home, and (7) have cable TV with box at home. The exclusion criteria are as follows: (1) inability to comply with study protocol (hearing/visual loss, cognitive impairment, etc); (2) absolute contraindication to exercise; (3) have cable TV operated by other companies than MEO, Vodafone, or NOS; and (4) have a household member involved in this study.

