All of the contents were disseminated on a dedicated channel through a TV app in a video format. As part of the motivation approach of our intervention program, brief reminders on health behaviors will also be diffused weekly through the TV app. These brief reminders will be powerful in recalling and stimulating study participants to adhere, encouraging lifestyle changes. Moreover, frequent contacts with participants are a relevant aspect of successful behavior change intervention programs [26], and follow-up monitoring is included in our program in order to monitor changes in specific behaviors and knowledge during the intervention period. With that purpose, short questionnaires will be delivered weekly through the TV. Thus, the interactive app will be used to collect data (short questionnaires) to evaluate the program compliance and learning. With these short questionnaires we aim to capture lifestyle changes and evaluate the learning along the intervention period. These questionnaires can easily be answered by pushing TV remote control buttons.

This 12-week TV-delivered program is composed by thematic weeks, and all of the contents (“nutrition and diet tips for healthy eating” videos, “healthy recipes” videos, brief reminders, and short questionnaires) developed for each week were specially designed to take into account the thematic week (Table 1).

**Table 1 table1:** Theme of each week of the interventional TV app on healthy eating and physical activity.

Week	Theme	Content
1	**Vegetable week**	
		Health benefits of vegetable consumption
		Recommendations for vegetable intake
		How to increase the daily intake of vegetables
2	**Water week**	
		Water, hydration, and health
		Recommendations for water intake
		Food resources that contain water
3	**Milk week**	
		Health benefits of consumption of milk and other dairy products
		Recommendations for milk intake
4	**Olive oil week**	
		Olive oil as a healthy cooking oil option
		Adequate amounts for using olive oil for food preparation and cooking
5	**Fruit week**	
		Health benefits of fruit consumption
		Recommendations for fruit intake
6	**Salt week**	
		Health risks of salt intake
		Recommendations for salt intake
		Foods with high and low salt content
		Strategies to reduce salt intake
7	**Meat, seafood, and eggs week**	
		Importance of consuming adequate amounts of meat, seafood, and eggs
		Adequate portions of meat, seafood, and eggs
		Healthier food options within the different foods of this group

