8	**Vegetable soup week**	
		Health benefits of vegetable soup consumption
		Standard recipe for a healthy vegetable soup
9	**Vegetable and fruit week**	
		Health benefits of vegetable and fruit consumption
		Recommendations for vegetable and fruit intake
		Meeting vegetable and fruit intake recommendations
		How choose the low cost options for these foods
10	**Healthy cooking week**	
		How to cook healthy food
11	**Sugar week**	
		Health risks of sugar intake
		Recommendations for sugar intake
		Foods with high and low sugar content
12	**Pulses week**	
		Health benefits of pulses consumption
		Recommendations for pulses intake
		How to include pulses in your diet daily intake

The themes for each week and consequently the contents of each video on nutrition and diet tips for healthy eating were chosen considering the main concerns on diet, in particular the main risk factors for noncommunicable diseases that are associated with unhealthy diets and the nutritional requirements for elderly people [27-29]. The low-cost healthy recipes are chef-created recipes and were specifically developed for our program by a popular Portuguese TV chef with a consulting nutritionist. The physical activity program was developed by physical exercise experts with the main goal of encouraging at least 30 minutes of physical exercise at home 3 times per week [30].

The delivery of these contents through the TV app will be scheduled for specific days of each week in order to develop a routine and constant program over the intervention period. Each day, 1 program will be available (Table 2). The TV app was developed by an external company, and the main TV cable operators agreed to disseminate this app.

**Table 2 table2:** Weekly schedule of the intervention delivery.

Weekday	Hour	Program delivery
Monday	2:00 PM	Nutrition and diet tips for healthy eating
Tuesday	12:00 PM	Healthy and low-cost recipes
Wednesday	9:00 AM	Physical exercise program
Thursday	2:00 PM	Brief reminder
Friday	Not fixed	Questionnaire
Saturday	Not fixed	Questionnaire
Sunday	—	—

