### Outcome Measures

The primary outcome assessed will be the changes in participant food insecurity score (evaluated by the HFIS) from baseline to 3 months. Secondary outcomes at 3 months will be changes in dietary habits (evaluated by 2-day 24-hour recall, PREDIMED index [31], and food frequency questions), changes in indicators of nutritional status (body mass index [BMI] and albumin and prealbumin levels), changes in muscle strength improvement (evaluated by dynamometer), changes in quality of life (EQ-5D-3L) [33], changes in fatigue scale (FACIT-F) [34], changes in serological markers of cardiovascular risk (insulin resistance, cholesterol levels, hemoglobin A_1c_, high sensitivity C-reactive protein, adipocytokines, interleukin 1, interleukin 6, and tumor necrosis factor), changes in physical activity (EMS [32] and IPAQ [35]); changes in body composition balance evaluated by bioimpedance, changes in inpatient admissions and outpatient appointments, changes in falls, and changes in knowledge regarding healthy lifestyle.

The secondary outcomes at 6 months will be changes in participant food insecurity score, changes in dietary habits (2-day 24-hour recall, PREDIMED index [31], and food frequency questions), changes in quality of life (EQ-5D-3L) [33], changes in fatigue scale (FACIT-F), changes in physical activity (IPAQ) [35], changes in inpatient admissions and outpatient appointments, changes in falls, and changes in knowledge regarding healthy lifestyle.

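### The sign of the whole-arm difference in mean BMI change does not by itself show improved nutrition; adjust for baseline BMI and report the arm difference by baseline BMI category

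*Protocol article*

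**What the plan says.** The Introduction hypothesises that the programme "will improve food security as well as clinical endpoints such as nutritional status, body composition, balance, strength, and quality of life". Outcome Measures lists among the 3-month secondary outcomes "changes in indicators of nutritional status (body mass index [BMI] and albumin and prealbumin levels". Data Analysis names nutritional status among the effects to be assessed, gives two-tailed t tests for change within each arm, and adds: "Independent sample *t* tests will be used to compare the intervention group and control group on the same outcomes".

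The population is not restricted by BMI. The Eligibility section has no BMI criterion; its first exclusions are "inability to comply with study protocol (hearing/visual loss, cognitive impairment, etc); (2) absolute contraindication to exercise". The Introduction describes both ends of the range. It reports that "more than one-third of Portuguese adults with food insecurity are overweight (41.0% in moderate food insecurity and 37.7% in severe food insecurity categories", and it says that "the concept of food insecurity in elderly persons also includes nutritional deficits". Table 1, in Description of the Intervention, covers adequacy ("Importance of consuming adequate amounts of meat, seafood, and eggs") as well as restriction ("Health risks of sugar intake").

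The article does not say whether a rise or a fall in BMI counts as improvement. The regression models in Data Analysis choose covariates by P value or clinical relevance, followed by backward selection. Baseline BMI is not named, and no reporting by BMI category is described.

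**The concern.** An outcome offered as evidence of improvement needs a favourable direction. For albumin and prealbumin, the Introduction's concern with deficits suggests one. For BMI it does not: a fall is plausibly good for an overweight participant and plausibly bad for a thin one. A programme that teaches both adequacy and restriction could move people either way.

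As planned, a difference in mean BMI change could be reported without showing whether it arose in overweight, normal-weight or thin participants. A difference in either direction could then be described afterwards as better nutrition.

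**Working it through.** **1. The plan's own figure.** The article gives no calculation for BMI. Its sample size is for the food insecurity score: difference 0.5, SD 1.5, power 0.80, alpha 0.05. The two-sided normal approximation gives n = 2 × (1.960 + 0.842)² × (1.5/0.5)² = 2 × 7.849 × 9 = 141.3, that is 142 per arm. Power at 141 is 0.799. The stated 141 per arm is reproduced and the BMI point does not touch it.

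**2. Inputs for BMI.**
- From the article: 141 per arm; overweight share p of 37.7% to 41.0%. These shares are for adults of all ages in severe and moderate food insecurity.
- Overweight per arm: 141 × 0.377 = 53 and 141 × 0.410 = 58.
- Assumed: effects of 0.5 kg/m2, SD of BMI change 1.0 kg/m2, no dropout, and a thin share of 10% where used. The article gives none of these.

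**3. What the whole-arm mean can show.** The arm difference is the sum of (share × effect) over baseline categories.
- A loss of 0.5 in overweight participants only: −0.5 × 0.377 = −0.1885, or −0.5 × 0.410 = −0.205.
- A loss of 0.1885 in every participant also gives −0.1885. So does a loss of 0.5 confined to 37.7% of participants who are not overweight.
- Overweight participants lose 0.5 and 10% are thin. If the thin gain 0.5, the difference is −0.1885 + 0.05 = −0.1385 to −0.205 + 0.05 = −0.155. If the thin lose 0.5, it is −0.2385 to −0.255.

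All these differences are negative, although their clinical meaning differs. The sign does not reveal which pattern occurred.

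**4. Precision by category.** The half-width of the 95% CI is t(0.975; 2n − 2) × SD × √(2/n), with SD 1.0:

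| Group | n per arm | Half-width, kg/m2 |
|---|---|---|
| Whole arm | 141 | 1.968 × 0.1191 = 0.234 |
| Overweight, 41.0% | 58 | 1.981 × 0.1857 = 0.368 |
| Overweight, 37.7% | 53 | 1.983 × 0.1943 = 0.385 |
| Thin, if 10% | 14 | 2.056 × 0.3780 = 0.777 |

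In 14 thin participants per arm, power for a difference of 0.5 is 0.247.

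**5. Does the category analysis gain power?** Two-sided t test, alpha 0.05, SD 1.0:
- Effect of 0.5 in overweight participants only: whole-arm power 0.351 to 0.404, overweight category 0.722 to 0.761 (0.557 to 0.604 if alpha is split over three categories). At SD 1.5 the whole arm has 0.183 to 0.208 and the category 0.398 to 0.429 (unsplit alpha).
- Effect of 0.5 in everyone: whole-arm power 0.987, overweight category still 0.722 to 0.761.
- Effect of 0.5 in overweight participants only, but 70% overweight (assumption): whole arm 0.83, category 0.86 with split alpha.

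A gain appears only if the effect is confined to overweight participants, and it nearly vanishes if they are the majority. Power is therefore not a reason for the change.

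**The case against.** The strongest reply is that nothing here is wrong. The t test is valid for a difference in means, and the article does not commit to reading a fall or a rise in BMI as improvement. Baseline adjustment and subgroup tables are details that a condensed article may leave to an analysis plan. Fat mass, fat-free mass, albumin, prealbumin and muscle strength are all measured at 3 months and help interpretation. Baseline BMI could enter the regression models as clinically relevant.

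Most of this stands, and it keeps the point small. What remains is that the article links BMI change to a hypothesis of improvement and names a comparison whose sign does not map onto improvement. The companion measures are compared by whole arm too. A baseline covariate, even if retained, gives no effect by category.

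The objection also limits the remedy. Baseline adjustment brings a little precision and does not settle the sign. Participants within the range have no favourable direction. Poor nutrition is not the same as low BMI, so categories make the result easier to read without resolving it for each person.

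A reader might go further and infer that benefit in overweight and thin participants would cancel or reverse the mean. The documents do not support this. With equal and opposite effects of 0.5, the sign flips only if the thin share exceeds the overweight share, about 38% to 41% here, and no thin share is given. Larger reversals require counting weight gain as benefit in everyone who is not overweight, which the article does not say. A reader might also infer a general gain in power, which step 5 of the working rules out.

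**Conclusion.** The point holds as a limit on interpretation: the sign of the whole-arm difference in mean BMI change cannot alone be taken as better or worse nutrition. The planned test is not in error. The matter concerns one of three indicators of one secondary outcome, and the change is optional.

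The conclusion rests on the absence of a BMI limit, the description of both overweight and deficits, and the lack of a stated favourable direction. How much it matters in practice is not established. The overweight shares come from adults generally and leave out the low food insecurity level, where Sample Size places most food-insecure households. The effects, SDs and thin share in the working are assumptions.

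**What to change.** In Data Analysis:
- Compare BMI at 3 months between arms with a linear model adjusted for baseline BMI, named in advance and not subject to covariate selection.
- State that the sign of this difference alone will not be interpreted as better or worse nutrition.
- Report the between-arm difference with 95% CI descriptively by baseline BMI category: below, within and above an age-appropriate range fixed before analysis. Read a fall as favourable only above the range and a rise as favourable only below it, and assign no direction within it. Use the between-arm contrast, because change within an arm among people selected by baseline BMI is distorted by regression to the mean.
- Label the category results exploratory and leave the other nutritional, body composition and strength comparisons as they are.

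The cost is wording only, since Data Collection already schedules height and weight at baseline and 3 months. The downside is the wide category intervals shown in the working, widest in thin participants, and a few more rows in an already long list of secondary results.
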